### Ethics

Permission to perform the study was obtained from the Ethics Committee of the University Hospital of Ghent (Belgium). Written consent for participation is obtained from all participants. Participation in the study is voluntary and all participants are informed that the data analysis will be anonymous and that they could withdraw from the study at any time. A reward (pedometer) for the participants in the intervention group who completed the program was foreseen.

## Baseline study population characteristics

A schematic overview of the recruitment process is shown in Figure 3. Twenty-five SHOs were interested to participate. Fourteen of these expressed a preference to serve as intervention group, while five preferred to serve as control group. Six expressed no preference neither for the intervention nor for the control group. These six were randomly assigned to the intervention group (n = 2) and to the control group (n = 4). In one of the SHOs serving as controls no patients were interested to participate.

**Figure 3 F3:**
[figure not shown]
Health promotion intervention: Recruitment process.

On the individual level 324 patients were willing to participate, including 225 and 99 candidates in respectively the intervention and control SHOs. This accounted for a response rate of 24% in the intervention group and 21.1% in the control group. Eleven respondents were excluded because of age (n = 2), cognitive impairments (n = 4), having a gastric ring placed (n = 1), and the impossibility to be weighed using the digital weighing scale (n = 4). Of these four patients, three had a pacemaker and one patient had an artificial limb. Twenty-nine (9.3%) of the remaining 313 candidates withdrew before the baseline measurement due to hospital admission (n = 4), no further interest (n = 24), and one patient died in the period prior to the baseline measurement. This resulted in 284 patients for whom baseline data are available.

The sociodemographic characteristics for the overall study population and by treatment group are listed in Table 1. The overall study population consisted of 174 men (61.3%) and mean age at enrollment was 46.3 years. Two-thirds of the patients (67.7%) were living together. Sixty-one percent of the participants were daily smokers and 46% used alcohol on a regular basis. The most frequent psychiatric diagnosis consisted of schizophrenia (37.9%), followed by mood disorders (24.5%). Mean baseline body weight was 87.1 kg. Sixty point three percent of men had a baseline WC of >102 cm. In women, 86.4% had a WC of >88 cm. Of the total sample, 33.4% were classified as overweight and 47.2% as obese (Table 2).

**Table 1 T1:** Baseline sociodemographic data

**Variable**	**All (n = 284)**	**Intervention group (n = 201)**	**Control group (n = 83)**	***p***
Sex				.27§
men, *n (%)*	174 (61.3)	119 (59.2)	55 (66.3)	
women, *n (%)*	110 (38.7)	82 (40.8)	28 (33.7)	
Age (years), *mean ± SD*	46.3 ± 12.3	46.2 ± 12.5	46.5 ± 11.9	.83‡
Smoking status, *n (%)*				.22§
no smoking	103 (39)	77 (41.4)	26 (33.3)	
smoking	161 (61)	109 (58.6)	52 (66.7)	
Alcohol use, *n (%)*				.81§
regular	122 (46)	87 (46.5)	35 (44.9)	
never	143 (54)	100 (53.5)	43 (55.1)	
Employment, *n (%)*				.51§
regular	13 (4.9)	11 (5.9)	2 (2.5)	
sheltered	105 (39.6)	73 (39.2)	32 (40.5)	
no	147 (55.5)	102 (54.8)	45 (57.0)	
Living situation, *n (%)*				<.05§
alone	86 (32.3)	71 (38)	15 (19)	
with others	180 (67.7)	116 (62)	64 (81)	
Stay in SH (years), median *(range)*	4 (0.1–22.3)	4.4 (0.1–22.3)	2.5 (0.1–16.3)	<.05†
DSM-IV diagnosis, *n (%)*				
schizophrenia	105 (37.9)	80 (41.2)	25 (30.1)	.08§
mood disorder	68 (24.5)	44 (22.7)	24 (28.9)	.27§
substance misuse	44 (15.9)	30 (15.5)	14 (16.9)	.77§
personality disorder	40 (14.4)	29 (14.9)	11 (13.3)	.71§
other	20 (7.2)	11 (5.7)	9 (10.8)	.13§
Medication, *n (%)*				
sedatives/anxiolytica	7 (2.8)	3 (1.7)	4 (5.7)	.09§
antipsychotics	56 (22.8)	46 (26.1)	10 (14.3)	.05§
antidepressants	12 (4.9)	8 (4.5)	4 (5.7)	.70§
sedatives/antipsych./antidepres.	49 (19.9)	31 (17.6)	18 (25.7)	.15§
sedatives/antipsychotics	20 (8.1)	16 (9.1)	4 (5.7)	.38§
sedatives/antidepressants	16 (6.5)	9 (5.1)	7 (10.0)	.16§
antipsychotics/antidepressants	75 (30.5)	58 (33.0)	17 (24.3)	.18§
no medication	11 (4.5)	5 (2.8)	6 (8.6)	

§Pearson Chi-Square.

‡Independent samples *t*-test.

†Mann–Whitney *U* test.

SH, sheltered housing; DSM-IV, Diagnostic and Statistical Manual of Mental Disorders.

**Table 2 T2:** Baseline anthropometric data

**Variable**	**All (n = 284)**	**Intervention group (n = 201)**	**Control group (n = 83)**	***p***
Weight mean ± SD *(kg)*	87.1 ± 19.5	87.9 ± 20.7	85.2 ± 16.0	.23‡
BMI mean ± SD *(kg/m²)*	30.0 ± 5.9	30.2 ± 6.1	29.5 ± 5.4	.37‡
Waist circumference mean ± SD *(cm)*	105.9 ± 16.1	106.2 ± 16.8	105.2 ± 14.4	.65‡
men wc >102cm, *n (%)*	105 (60.3)	76 (63.9)	29 (52.7)	.16§
women wc >88 cm, n (%)	95 (86.4)	70 (85.4)	25 (89.3)	.60§
Fat mass mean ± SD *(%)*	33.9 ± 10.6	34.2 ± 10.5	33.4 ± 10.6	.57‡
BMI class, *n (%)*				.70§
underweight (<18.5)	3 (1.1)	3 (1.5)	0 (0)	
normal weight (18.5–24.9)	52 (18.3)	36 (17.9)	16 (19.3)	
overweight (25–29.9)	95 (33.4)	66 (32.8)	29 (34.9)	
obesity (≥30)	134 (47.2)	96 (47.8)	38 (45.8)	

§Pearson Chi-Square.

‡Independent samples *t*-test.

kg., kilogramme; BMI, Body Mass Index (kg/m²); WC, waist circumference.

No statistical significant difference between the intervention and the control group was found for the primary outcome variables ‘body weight’ (p = .23), BMI (p = .37), WC (p = .65) and fat mass (p = .57). No statistical significantly differences were observed between the intervention and control group for the sociodemographic variables, except for the variables ‘living situation’, and ‘duration of stay in sheltered housing’. Length of stay in sheltered housing was significantly longer in participants in the intervention group (median 4.4 vs. 2.5, p < .05). A statistically higher proportion of controls was living together compared with those in the intervention group (81 vs. 62%, p < .05). Psychotropic medication use was found to be statistically different between the two groups for only the antipsychotics (p = .05).

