### Study population

The study population consisted of people with MD aged between 18 and 75 years living in a SHO in the Flanders region (Belgium). There are 42 SHOs in the Flanders region, including 2662 approved places [23]. Exclusion criteria included people aged <18 or older than 75 years, having a gastric ring or pacemaker placed, having cognitive impairments (assessed by the mental health professionals) compromising the understanding of the psycho-educational and behavioral sessions of the health promotion intervention.

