### Data analysis

Parametric and non-parametric tests are used at the individual level to compare the intervention and control group at baseline, depending on the distributions of the quantitative variables. The X²-test is used in qualitative variables. Repeated measure analyses will be used to evaluate differences in the primary outcome variables body weight, BMI, WC and fat mass between pre- and post-intervention in the intervention and control group. Because preference randomization occurred at the level of SHO and not at the level of the individual patient, cluster effects will also be examined. The analyses of the primary outcomes will be performed on an intention to treat (ITT) basis. Secondary outcome variables will be evaluated per protocol. A P-value ≤0.05 is considered statistically significant. For statistical analyses, SPSS®19 will be used.

To examine the cost-effectiveness of the intervention, a Markov decision-analytic model assuming a public payer perspective will be constructed to project health outcomes and costs of the health promotion intervention compared with usual care. Overweight and obesity are substantial risk factors for the high prevalence of type 2 diabetes and cardiovascular disease in individuals with MD[35,36]. Therefore, the Markov model will be used to estimate, for both the intervention and control group, the development of cardiovascular disease and type 2 diabetes over time and the associated costs. The time horizon will be a 10-year period. In both the intervention and control arm several health states will be included in the Markov model. All future costs and health outcomes will be discounted respectively at 3% and 1.5% annually. The costs will be calculated by analyzing the direct health care costs and the costs of the program. The direct health care costs include hospitalization, medication, GP consultations, and other health professionals costs. The program related resource use (staff time, materials) and resulting costs will be calculated making a distinction between the resource used and costs related to the research purpose and those related to the intervention itself.

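### Most organisations chose their arm, and the stated primary analysis uses none of the three baseline imbalances the article reports: length of stay, living situation and antipsychotic use

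*Protocol article*

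**What the plan says.** **Allocation.** The section on baseline study population characteristics reports that 25 SHOs took part. "Fourteen of these expressed a preference to serve as intervention group, while five preferred to serve as control group". Only six had no preference: "These six were randomly assigned to the intervention group (n = 2) and to the control group (n = 4").

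**Imbalances.** The text after Table 2 reports "Length of stay in sheltered housing was significantly longer in participants in the intervention group (median 4.4 vs. 2.5, p < .05") and "A statistically higher proportion of controls was living together compared with those in the intervention group (81 vs. 62%, p < .05"). It also flags antipsychotics, at p = .05. The Discussion names the same three variables as the only ones that differ and draws no consequence for the analysis.

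**Primary analysis.** The Data analysis section says "Repeated measure analyses will be used to evaluate differences in the primary outcome variables body weight, BMI, WC and fat mass". The two arms are compared on values before and after the programme, by intention to treat, and the section adds that "cluster effects will also be examined". It names no covariate and no distinction between SHOs that chose their arm and those that were randomised.

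**The concern.** In a fully randomised trial, a baseline imbalance is a chance event that the test already allows for. Here about three quarters of the clusters selected themselves, so an imbalance may reflect which kind of organisation volunteers for which arm. It would then be a systematic difference between the arms.

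A repeated-measures comparison of change takes out a difference in starting level. It does not take out a difference in trend. If residents with shorter stays, shared housing or antipsychotic treatment would change weight differently over 36 weeks without the programme, part of that difference is credited to the programme or hidden by it. Examining cluster effects deals with correlation within SHOs, which concerns the standard error and not this bias. For the same reason, the non-significant baseline comparisons of weight, BMI, waist circumference and fat mass do not settle the matter.

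**Working it through.** **1. Share of clusters allocated by preference** (counts from the recruitment text)
- Preference: 14 + 5 = 19 of 25 = 76%. Randomised: 6 of 25 = 24%.
- By arm: intervention 14 of 14 + 2 = 16; control 5 of 5 + 4 = 9. One control SHO yielded no participants.

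**2. Living situation** (Table 1)
- With others: intervention 116/(71 + 116) = 116/187 = 62.0%; control 64/(15 + 64) = 64/79 = 81.0%. The difference is 19.0 points.
- Pearson chi-square = N(ad − bc)²/(product of margins) = 266 × (71×64 − 116×15)²/(187 × 79 × 86 × 180) = 9.15, p = 0.0025. The article's p < .05 is reproduced.
- The article's baseline tests ignore clustering: "Parametric and non-parametric tests are used at the individual level to compare the intervention and control group at baseline". Dividing by the article's own design factor of 1.5 gives 9.15/1.5 = 6.10, p = 0.014. With a factor of 2.0, p = 0.032; with 2.5, p = 0.056.

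**3. Antipsychotic use** (Table 1)
- Antipsychotics only: 46/176 = 26.1% vs 10/70 = 14.3%; chi-square 4.00, p = 0.045, which agrees with the stated .05.
- Table 1 splits medication into exclusive combinations, so this row misses most users. Summing every row that contains an antipsychotic: intervention 46 + 31 + 16 + 58 = 151 of 176 = 85.8%; control 10 + 18 + 4 + 17 = 49 of 70 = 70.0%. The difference is 15.8 points; chi-square 8.22, p = 0.004.

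**4. Length of stay** (Table 1)
- Medians 4.4 vs 2.5 years; ranges 0.1–22.3 and 0.1–16.3. The Mann–Whitney test cannot be recomputed from medians and ranges.

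**5. Possible size of the bias**
- For a binary factor, shift in the arm contrast = difference in prevalence × difference in weight change between its two levels. The documents give no figure for the second term, so 1–3 kg is an assumption.
- Living situation: 0.19 × 1 = 0.19 kg to 0.19 × 3 = 0.57 kg, which is 5% to 16% of 3.5 kg.
- Any antipsychotic, same assumption: 0.158 × 1 = 0.16 kg to 0.158 × 3 = 0.47 kg.
- To produce the whole 3.5 kg, housing types would have to differ by 3.5/0.19 ≈ 18 kg in weight change.
- The factors may add or offset, and no direction can be given.

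**6. Missing covariates**
- Living situation: 284 − (187 + 79) = 18. Medication: 284 − (176 + 70) = 38. The number with length of stay missing is not given.

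**The case against.** The strongest objection is that the Data analysis section is silent on covariates and does not say the analysis is unadjusted. A journal article often leaves a covariate list to a fuller plan, and that plan may exist. This stands as a limit: nobody can say from the article that the final analysis will be unadjusted. It does not dispose of the point. The article was written with the baseline data in hand, reports the imbalances twice, and still describes the primary analysis in the future tense, down to analysis set, significance level and software, without using them.

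Second, the article links stay and housing to arm, not to weight change. That also stands, so they are potential confounders only. For antipsychotics the article supplies a link itself: its Background names their side effects on body weight.

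Third, the plausible shift is modest against 3.5 kg. That is so on the assumption used here.

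A reader might go further and infer that the control arm holds more newly admitted residents, that their weight is still drifting after admission, and that eligibility should have required a minimum stay. The documents do not support this. Eligibility is simply "The study population consisted of people with MD aged between 18 and 75 years living in a SHO in the Flanders region (Belgium"), which is a legitimate resident population. The shortest stay is 0.1 years in both arms, the number of recent admissions is not reported, and a control median of 2.5 years means that at least half had lived there that long or longer. Nothing is said about weight change after admission. For the same reasons, a sensitivity analysis restricted to stays above some cut-off, such as six months, has no basis in the article.

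**Conclusion.** The concern holds in a limited form. Under allocation that was 76% by preference, three acknowledged baseline imbalances play no part in the primary analysis as stated, and comparing change does not protect against differing trends. Any bias is of unknown direction. On an assumed 1–3 kg difference in weight change, living situation alone would shift the contrast by about 0.2–0.6 kg and antipsychotic use by about 0.2–0.5 kg. This could alter an estimate near the margin but is unlikely to create the whole planned effect. The imbalances do not show that the trial result will be biased. The case for acting is that adjustment is cheap, and that covariates chosen after the outcomes are seen are open to challenge.

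**What to change.** In the Data analysis section, before the 10- and 36-week outcomes are analysed, specify the following:
- For all four primary outcomes, fit the repeated-measures model with SHO as the cluster.
- Include length of stay, living situation and any antipsychotic use as baseline covariates, each with its interaction with time. Main effects alone adjust the level of weight, not its trend.
- Show the unadjusted result alongside.
- Add a sensitivity analysis that includes whether the SHO was allocated by preference or by randomisation. With only six randomised SHOs it will be imprecise and should be read as such.
- State how missing covariates are handled, for example by multiple imputation. Otherwise complete-case adjustment would drop between 38 and 18 + 38 = 56 of 284 participants (13% to 20%) for living situation and medication alone, which sits badly with intention to treat.

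**Cost:** a little more analysis work and the missing-covariate step. No new data are needed, because Table 1 shows that all three variables were recorded. Adjustment covers only these measured factors. Other differences between organisations that chose different arms would remain, and the report should say so.

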## Discussion

In this paper the study design and baseline characteristics of a health promotion intervention targeting PA and healthy eating in people with MD living in sheltered housing is described. At baseline, statistical analysis of the characteristics found only a significant difference between the intervention and the control group for the variables ‘living situation’, ‘duration of stay in sheltered housing’, and antipsychotic medication use.

The baseline characteristics demonstrate the unhealthy condition of the study population. A higher prevalence of overweight and obesity was found in the study population compared with the general population in Belgium. Eighty percent of the study population has a BMI of >25 of which 47% is classified as obese, compared with respectively 47 and 14% in the general population [37]. Smoking prevalence in the study population also exceeds that of the general population in Belgium. Amongst the study population, 61% are daily smokers compared with 21% in the general Belgian population [37]. According to the results of several studies, the measurement of the WC and waist-hip ratio is more appropriate than measuring the BMI to estimate the risk for future cardiovascular events [38,39]. A WC above 102 cm for men and 88 cm for women is associated with an increased risk of developing health problems such as cardiovascular disease, type 2 diabetes and hypertension [30]. Sixty percent of men and 86% of women in our study population had a baseline WC above this threshold.

Given the high burden of overweight and obesity in people with MD, research on the effectiveness and cost-effectiveness of lifestyle interventions in this population is of substantial importance. Yet, there are several challenges in setting up trials involving individuals with MD. Previous research has identified a number of barriers to engagement in health promotion programs like the MD itself, side effects of psychotropic medication, financial barriers, poor motivation or unwillingness to participate, and absence of support [40-42].

According to the results of previous research on the effectiveness of weight management interventions in mental health care, significant reductions in weight gain are possible [43,44]. The results of these trials must however be interpreted cautiously because they are frequently limited by small sample sizes and short intervention periods. It is nevertheless promising that small weight reduction in this population is possible.

As far as known to the authors, this is the first trial evaluating both the effectiveness and cost-effectiveness of a health promotion intervention targeting PA and healthy eating in mental health care. Cost-effectiveness evaluations have a great social value as health promotion and prevention have an economic cost, but they can also increase healthy life expectancy and save money because diseases and complications can be avoided.

It is likely that the results of this intervention in SHOs will lead to further health promotion programs targeting other populations in mental health care, such as inpatients.

## Abbreviations

BMI, Body Mass Index; BSI, Brief Symptom Inventory; WC, waist circumference; GP, general practitioner; I, intervention; ICC, intraclass correlation coefficient; ICER, incremental cost-effectiveness ratio; IPAQ, International Physical Activity Questionnaire; ITT, intention to treat; kg, kilogramme; MD, mental disorder; NI, no intervention; PA, physical activity; QALY, quality-adjusted life year; QOL, quality of life; SHO, sheltered housing organisation; vs., versus.
